**Figure 1 fig1:**
[figure not shown]
Flow chart of data acquisition. T0a, Baseline assessment; T0b, Second baseline after four individual sessions; T6-T12, 6 months outcomes assessments; T-END, final assessment, occurring at any time between T6 and maximum at T18, based on therapy duration.

Standardization will be promoted through clinician training workshops, adherence to a unified EMDR therapy protocol, and regular feedback sessions to ensure data consistency among therapists and patients.

We will report results according to the CONSORT Extension for N-of-1 Trials (Vohra et al., 2016), adapted for the observational, non-randomized design. Items related to randomization, allocation concealment, or predefined treatment sequences will be marked as not applicable. To ensure transparent reporting of observational aspects, the CENT checklist will be used in combination with STROBE (Vohra et al., 2016; von Elm et al., 2008).

This study has been approved by the Ethical Committee of the University of Torino (approval number 0565145) and it has been registered at ClinicalTrials.gov (ID: NCT07033741).

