RQ			X										X	
PDS^5^										X		X		X
Recalled Memory Evaluation^6^							X		X		X		X	
Resource and Event Assessment^7^								X						

1 Pre-session: before each session.

2 Post-session: at the end of each session.

3 P: Patient.

4 T: Therapist.

5 Completed by the therapist after the first four EMDR sessions and at T6, T12, and T-END.

6 Completed by the patient before and after EMDR processing sessions targeting one of their top 10 traumatic memories (selected during assessment, EMDR phase 3) or newly identified core negative events (EMDR phases from 1 to 3).

7 Completed by the therapist after each therapy session.

BDI-II, Beck Depression Inventory; PHQ-9, Patient Health Questionnaire-9; PID-5-BF, Personality Inventory for DSM-5 – Brief Form; PBS-R, Pathogenic Beliefs Scale-Revised; GAD-7, Generalized Anxiety Disorder-7; DES-II, Dissociative Experiences Scale; MDI, Multidimensional Dissociation Inventory; PITQ, Progress in Treatment Questionnaire; PCL-5, Post-traumatic Stress Disorder Checklist; DERS, Difficulties in Emotion Regulation Scale; MSQ, Mini Sleep Questionnaire; WAI, Working Alliance Inventory; LSC-R, Life Stressor Checklist-Revised; CEAS, Compassionate Engagement and Action Scales; PHLMS, Philadelphia Mindfulness Scale; RQ, Relationships Questionnaire; PDS, Processing Difficulties Scale.

Following baseline assessments (T0a and T0b), additional assessments at 6 months (T6), 12 months (T12), with a maximum follow-up period of 18 months (T18) will be used to monitor changes in symptomatology, physical and emotional functioning, and other potential predictive factors. If therapy concludes before T18, the final assessment will be conducted at that time point as a comprehensive post-treatment follow-up to ensure all outcome measures are captured.

From T0b onward, pre-session and post-session data collection will capture detailed longitudinal records of therapy progress. Before each therapy session, patients will complete questionnaires assessing anxiety and depression symptoms and tracking changes in traumatic memories on account of treatment. After each session, therapists will document session-specific data, including process-related factors and specific features of the EMDR session, such as the therapeutic target, the technique of bilateral stimulation used, and the subjective units of distress. Potential adverse events in the patient’s life (e.g., self-harm and suicidality) between treatment sessions are also recorded.

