### Treatment

2.5

Participants will receive EMDR therapy in accordance with standardized clinical protocol (Hofmann et al., 2015; Shapiro, 2018). In line with the real-world nature of this study, the number of EMDR sessions will not be *a priori* defined. However, after each session, therapists will specify the session type (EMDR or non-EMDR) in REDCap. Therapists will exercise clinical judgment in selecting session type, and the exact session date, type, and key contextual variables (e.g., symptom severity, medication changes, major life events) will be recorded to permit adjustment for time-varying confounding in the analysis.

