### Sample size estimation

2.6

There is no established method for estimating sample size on N-of-1 trial designs in observational settings. Following Senn’s (2019) recommendations, and the practical guidance of Yang et al. (2021), at least 32 therapist-patient dyads, with a minimum of 26 visits per participants, approximately 1 visit/week for 6 months. Yang et al. suggests that roughly 24 repeated measurements per individual provide reasonable power to detect a moderate within-patient effect (Cohen’s d around 0.5), when aggregating results across multiple N-of-1 series. We expect a small number of patients to record fewer than 24 outcome measurements. However, since follow-up can extend up to 18 months, some patients will likely record considerably more measurements. Moreover, because the Bayesian hierarchical model naturally down-weights individual patients with less precise within-patient estimates, participants with fewer observations will contribute less to the pooled effect. As a result, a small number of shorter series should not materially reduce the precision of the overall estimate.

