Session-level outcomes (PHQ-9 scores) are nested within patients. The model will include patient-specific random intercepts and random slopes for the EMDR effect. To model temporal dependence, residuals at the session level will incorporate an AR(1) structure, capturing correlation between consecutive measurements within each patient. Weakly informative priors will be used for all regression coefficients (Normal[0,5]) and for the standard deviations of random effects (half-Normal[0,2]), while the AR(1) correlation parameter will have a uniform prior on (−1,1). Missing session-level outcomes will be handled directly within the hierarchical framework under a missing-at-random assumption, allowing all available repeated measurements to contribute to estimation. Patients with fewer sessions will be naturally down-weighted via partial pooling, without the need for imputation. Sensitivity analyses will explore alternative residual correlation structures (e.g., ARMA[1,1]), inclusion/exclusion of patients with very few sessions, and adjustment for time-varying covariates to assess potential confounding. Model convergence will be assessed through trace plots, $\hat{R}$statistics ($\hat{R}$≤1.01), and effective sample size for all parameters. Posterior predictive checks will be used to evaluate model fit and the adequacy of assumptions.

We will also perform secondary analyses using anxiety symptoms as outcome, and will evaluate the effect of other predictors and moderators (e.g., dissociation, post-traumatic symptoms, emotional dysregulation, and sleep difficulties). Missing sessions will be handled directly in the longitudinal model. Because the primary analysis uses a Bayesian hierarchical time-series model, missing outcome data are accommodated under a missing-at-random (MAR) assumption without requiring imputation or exclusion of the entire individual. Dropout will be recorded by therapists together with the stated reason, and dropout patterns will be summarized descriptively.

All analyses will be conducted using R version 4.5.0 (R Core Team, 2025).

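### Session type is chosen by therapist judgment, yet adjustment for time-varying confounding is only a sensitivity analysis and the stated primary model names no time term

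*Protocol article*

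**What the plan says.** The Treatment section of the protocol article leaves the choice of session to the clinician: "Therapists will exercise clinical judgment in selecting session type". The same sentence lists what is captured for each session: the date, the type, and context such as symptom severity, medication changes and major life events. It also gives the purpose. These data "will be recorded to permit adjustment for time-varying confounding in the analysis".

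The Study design section confirms that chance does not protect the comparison: "Items related to randomization, allocation concealment, or predefined treatment sequences will be marked as not applicable".

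The Statistical analysis section then describes the primary model for session-level PHQ-9: "The model will include patient-specific random intercepts and random slopes for the EMDR effect". Temporal dependence is handled by AR(1) residuals. Priors and convergence criteria are given. No term for time, session number or trend is named. Covariate adjustment appears in the list of sensitivity analyses, next to alternative residual structures: "inclusion/exclusion of patients with very few sessions, and adjustment for time-varying covariates to assess potential confounding".

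**The concern.** In a conventional N-of-1 trial, randomised periods separate the treatment contrast from the passage of time and from the patient's current state. This adaptation drops that protection, so the model has to replace it. The article recognises the problem and collects the data needed, but its headline estimate does not use them.

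Two routes to bias are plausible from the document.

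- **Time.** Patients enter with clinically significant symptoms in at least one domain and may improve regardless of session type. Sessions may focus on stabilisation, resource development or target processing, so the share of EMDR sessions may shift over a course of therapy.
- **Selection.** Symptom severity is a named contextual variable for a choice made by judgment, and PHQ-9 is completed before each session. If a score is paired with the type of the session that follows it, the score can be the reason for the session type as well as its supposed result. The article does not state which session a score is paired with.

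The primary objective is to predict who responds, so the patient-specific EMDR slopes matter as much as their mean. A slope that mixes response with timing or selection is a poor quantity on which to study predictors.

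**Working it through.** **1. The plan's own benchmark.** The Sample size estimation section asks for "at least 32 therapist-patient dyads, with a minimum of 26 visits per participants, approximately 1 visit/week for 6 months" and cites about 24 measurements and a Cohen's d of about 0.5. It gives no alpha, numeric power or SD, so no stated power figure can be reproduced. Assume two-sided alpha 0.05, independent errors and 12 sessions of each type.

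- One patient: power 23%; 63 sessions per condition would be needed for 80%.
- Pooled over 32 patients with slope SD τ (in residual-SD units): SE = √((τ² + 2/12)/32).
- τ = 0.5: SE = √(0.4167/32) = 0.114; 0.5/0.114 − 1.96 = 2.42; power 99%.
- τ = 1.0: SE = √(1.1667/32) = 0.191; 0.5/0.191 − 1.96 = 0.66; power about 74%.

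This agrees with the article's qualitative statement about aggregation. The issue is therefore bias, not precision. With an assumed residual SD of 3 PHQ-9 points, d = 0.5 is 0.5 × 3 = 1.5 points.

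**2. Simulation with a true EMDR effect of 0.** From the document: 32 patients, 26 sessions. Assumed:

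PHQ-9 = 14 + a_i − D_i × t/25 + e_it

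with SD(a) = 4, SD(e) = 3, AR(1) correlation 0.4, and mean decline D of 0, 5 or 8 points over the series (5/25 = 0.20 points per week; 8/25 = 0.32). The between-patient SD of the decline is 2 where D is above 0. For selection, the probability of EMDR is 1/(1 + exp(±0.4e)), using the deviation e at the same session. Fitting is by maximum likelihood as a stand-in for the Bayesian fit, with 15 replicates per scenario. The entries are mean estimated EMDR effects in PHQ-9 points; the truth is 0.

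| How session type arises | Decline | Stated model | With linear time added |
|---|---|---|---|
| Unrelated to time | 5 | +0.03 | +0.02 |
| No EMDR in first 4 sessions, then 60% | 5 | −0.17 | +0.03 |
| No EMDR in first 4 sessions, then 60% | 8 | −0.14 | +0.03 |
| None in first 4, then rising 10% to 90% | 5 | −0.48 | +0.02 |
| None in first 4, then rising 10% to 90% | 8 | −0.41 | +0.02 |
| Falling 90% to 10% | 5 | +0.34 | −0.04 |
| EMDR avoided when current severity is high | 0 | −2.21 | −2.21 |
| EMDR preferred when current severity is high | 0 | +2.22 | +2.22 |

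The stated model rejected at the nominal 5% level in 40–47% of runs in the two rising rows and in every run in the two severity rows. With 15 replicates these rates are rough: at 47%, the Monte Carlo SE is √(0.47 × 0.53/15) = 0.13. Unbiased scenarios themselves rejected in 7–13%.

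**3. A second set with 60 replicates** and the same sizes, residual SD and AR(1) gave −0.35 points (37% rejected) for a share rising 10% to 90% with a decline of 5, and −0.25 (33%) for 20% to 80%. Adding time gave +0.01 and −0.01 (8% each). Selection on current severity gave about −1.9 or +1.9, again unaffected by time.

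**4. What removes the selection bias.** In the 60-replicate set, taking the preceding session as the exposure and adding time left about ±0.07. Adding prior PHQ-9 as well left about ±0.2.

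**5. Role of the AR(1) term.** Its fitted correlation was 0.41 without a trend and rose to about 0.55–0.70 with one. It absorbs part of the decline, which is why the bias is no larger for a decline of 8 than for 5.

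**The case against.** The strongest reply is that this is a condensed article and its list of model terms is plainly incomplete. The same model is meant to assess personality domains and pathogenic beliefs, yet none of these appears in it. Priors are given for all regression coefficients without listing them. Session date is among the data recorded for adjustment, and the phrase about time-varying covariates could include time. So a reader might infer that time is excluded from every planned analysis, but the text does not establish this. What stands is narrower: no time term is named, and covariate adjustment is explicitly assigned to a sensitivity analysis. That assignment is a stated choice, not an omitted detail.

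A reader might also infer that the model will credit natural improvement and selection to EMDR. The document does not support this either. It gives no timing of EMDR sessions. The bias reverses if EMDR comes early or when patients are worse, and disappears if session type is unrelated to time and severity. Pre-session collection starts only at T0b, after four sessions, so some early change may precede the series, and the rows above with no EMDR in the first four sessions may overstate that mechanism. Eligibility needs only one of four symptom domains, so baseline depression need not be high.

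It would also be too strong to say that AR(1) residuals do nothing about a trend, or that the moderator results are certainly biased. Systematic moderator bias requires session timing or selection to be associated with the personality or belief scores. That was not simulated and is not shown.

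**Conclusion.** The concern holds as a conditional one. As written, the headline EMDR effect and the patient-specific slopes come from a model without the adjustment that the Treatment section says the data are collected for.

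Under the assumed inputs, trend alone can shift the estimate by about 0.2 to 0.5 PHQ-9 points in either direction, at most 0.48/3 = 0.16 residual SD. Selection on current severity is the larger risk: about 2 points, or 2.2/3 = 0.73 residual SD, which exceeds the 1.5 points that d = 0.5 represents at the assumed SD. That figure requires each score to be paired with the type of the same session, which the article neither states nor rules out. A time term corrects the first problem and leaves the second untouched.

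The residual SD, autocorrelation, decline, session timing and strength of selection are all assumptions. Direction and order of magnitude are usable; the exact rejection rates are not.

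**What to change.** Restate the primary model so that it includes:

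- time since first session, linear with a patient-specific slope, with a spline as a check;
- the recorded medication changes and major life events;
- the EMDR exposure defined as the type of the session preceding each pre-session PHQ-9, so that one score cannot be both the reason for a session type and the outcome attributed to it.

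Move the unadjusted model to the sensitivity analyses. Examine adjustment for prior PHQ-9 there too, and do not require it in the primary model: it is itself affected by earlier EMDR, and it interacts with the random intercepts and AR(1) errors.

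The cost is a change of wording in the analysis plan before analysis, since the variables are already being recorded. Intervals will be somewhat wider. Time may also absorb part of a slow, cumulative EMDR benefit, which is the reason to keep reporting the model without time alongside.

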## Discussion

3

The present study protocol is the first prospective observational design that combines multiple N-of-1 trials to investigate the predictors and process moderators of the efficacy of EMDR therapy for depressive symptoms. Previous studies have shown the importance of understanding how EMDR works when it is delivered under real-world conditions (Matthijssen et al., 2020). We intend to evaluate processing styles and their relationship with various indicators that may help improve clinical interventions (Ramallo-Machín et al., 2024) and contribute to bridging the current gap between research findings and clinical practice (Fernández-Álvarez et al., 2020).

The inclusion of patients presenting at least one or more of the clinical domains (e.g., anxiety, depression, dissociative, or post-traumatic stress symptoms) is strongly supported by evidence that these conditions are not separate entities but rather mutually influential systems that constitute an integrated network structure (Groen et al., 2020; Lazarov et al., 2020). This network is heavily defined by a general distress factor or negative affect that is common to depression, generalized anxiety disorder, and PTSD (Price et al., 2019). Depressive symptomatology is intrinsically linked to this structure. The inclusion of dissociation is also critical because it is another important condition that may influence the effectiveness of treatment in patients with anxious and depressive symptoms who are resistant to previous treatment (Prasko et al., 2016). A higher degree of dissociation at the beginning of the treatment predicted minor improvement in depression and anxiety symptom reduction, while the major therapeutic change is connected to greater reduction of the dissociation level (Fung et al., 2025; Prasko et al., 2016). Therefore, including these interacting domains is necessary to accurately explore factors associated with the EMDR treatment effect on depressive symptoms.

Through the integration of innovative methodologies using N-of-1 trials, meta-analysis and meta-regression, this study contributes to deepening our understanding of factors influencing the effectiveness of EMDR and its application in natural settings. Additionally, the design of our study offers the opportunity to explore both patient and therapist characteristics and process variables in real-world clinical settings, with a broad range of measures assessed on multiple occasions. Indeed, as Kazdin (2007) suggested, assessment on a session-by-session basis (i.e., every time before and after each session over the course of treatment) is useful for evaluating the mediator of change and symptom reduction and considering individual differences during these changes.

For our first objective, we expect that profiling individual psychological functioning at baseline will be associated with the severity of depressive symptoms at baseline and during EMDR therapy. Although several studies have examined the relationship between personality and mental health treatment (Bucher et al., 2019), the literature has shown a limitation in assessing personality dimensions only at the beginning of therapy (Samuel et al., 2018). For these reasons, we expect that collecting personality and pathogenic belief ratings at the end of therapy will have the potential advantage of capturing more data for therapists and allowing clearer prediction of longer-term treatment outcomes in clinical reality.

Moreover, the structure of our study supports real-world evidence through the longitudinal evaluation of other potential factors that potentially play an important role in adapting effectiveness of EMDR treatment. Indeed, these findings could inform a more nuanced understanding of the mediating role of individual and process factors of EMDR therapy in associations with depressive symptoms severity.

In line with the broader aim of this project, we expect that this study will represent a promising line of research that has been designed to advance clinical practice by enabling the systematic collection of real-world data and developing evidence-based strategies to optimize interventions based on individual patient characteristics. We believe that a more thorough understanding of the factors associated with the efficacy of EMDR therapy and treatment implications will enhance the evaluation of individual variability in treatment responses, offering critical insights into the factors underlying the effectiveness of EMDR therapy in depressive symptoms. Finally, through this collaborative effort between researchers and clinicians, we intend to promote and advance the quality and scientific evidence of EMDR in the treatment of depression by emphasizing the interplay between therapeutic processes and treatment outcomes within a real-world context.

## Trial registration and status

This study has been registered at Clinicaltrials.gov (ClinicalTrials.gov Identifier: NCT07033741). Data collection began in June 2025 and is currently ongoing. The study is expected to be completed by December 2027. The study timeline is presented in the Supplementary material.
